## Abstract

**Background:**

Research has shown that engaging in a range of healthy lifestyles or behavioral factors can help reduce the risk of developing dementia. Improved knowledge of modifiable risk factors for dementia may help engage people to reduce their risk, with beneficial impacts on individual and public health. Moreover, many guidelines emphasize the importance of providing education and web-based resources for dementia prevention. Internet-based interventions may be effective, but few have been studied rigorously or widely disseminated. We created DementiaRisk, an award-winning, web- and email-based education platform for the public focused on modifiable risk factors, featuring multimedia e-learning and email “microlearning” content, to help raise awareness and improve knowledge of actions to reduce dementia risk.

**Objective:**

This protocol describes a randomized controlled trial to (1) evaluate whether exposure to DementiaRisk changes knowledge of dementia risk factors, intention to engage in risk reduction activities, and health behaviors related to dementia risk reduction and to (2) explore qualitative aspects including participants’ engagement and satisfaction with the intervention and barriers and facilitators to use.

**Methods:**

Using a sequential explanatory mixed methods design, this study conducts a quantitative analysis followed by a qualitative inquiry to evaluate outcomes and feasibility. In total, 485 participants will be recruited on the web and randomly assigned to 2 groups: one accessing DementiaRisk and the other receiving alternative e-learning on mild cognitive impairment. Assessments will be delivered on the web at baseline (T1), at 4 weeks (T2), and at 2 months after the intervention (T3). Knowledge will be assessed using items from the Dementia Knowledge Assessment Scale, intentions to engage in risk reduction activities will be assessed using items in line with current evidence, and health behaviors related to dementia risk reduction will be assessed using items from the Godin-Shephard Leisure Time Physical Activity Questionnaire along with additional questions related to a range of health status domains. Outcomes and feasibility will be assessed using the Information Assessment Method for patients and consumers. A linear mixed effects model will be used to examine the relationship between each outcome score by group and time point.

**Results:**

This study was approved by the Hamilton Integrated Research Ethics Board on August 24, 2022 (project ID 14886) and received funding in February 2023. Recruitment took place from March 28, 2023, to April 28, 2023, with the final participants completing the intervention by August 18, 2023. Analyses and interpretation of data are ongoing.

**Conclusions:**

DementiaRisk is a readily scalable, technology-enhanced solution for dementia prevention education. It has been designed using evidence-based principles of multimedia learning. It has the potential to scale and spread widely using the open internet, so it may be able to reach a wider audience than traditional in-person educational interventions.

**Trial Registration:**

ClinicalTrials.gov NCT05383118; https://clinicaltrials.gov/study/NCT05383118

**International Registered Report Identifier (IRRID):**

DERR1-10.2196/64718

## Introduction

### Background

Developing a better understanding of how dementia can be prevented and sharing information about how Canadian people can reduce their risk of developing dementia or delay its onset are critical to keeping Canadian people healthy and improving their quality of life. The Landmark Study, which developed evidence-based data modeling to demonstrate the impacts of improving risk reduction efforts to delay onset across the population, suggests that a delay of 1 year could result in nearly 500,000 fewer cases of dementia by 2050 [1]. Additionally, if dementia prevention efforts can delay the onset of dementia by 10 years, then over 4 million new cases of dementia could be avoided by 2050 [1]. Web-based learning about the promotion of brain health is a readily scalable, technology-enhanced solution for dementia risk prevention education. Web-based learning has the potential to reach a wider number of audiences with modifiable risk factors for dementia than traditional face-to-face interventions.

While there have been studies of web-based health information on intentions and behavior change, most of those studies have looked at text-based health information rather than internet-based interventions that have incorporated best practices in instructional design for e-learning. Most of the web-based content about modifying dementia risk factors currently is text based, such as static web pages or pamphlets or booklets. Of the few multimedia e-learning courses available, some require a substantial commitment (eg, weeks long), are synchronous (ie, require real-time participation), are associated with a commercial entity or product for sale, or have a cost associated with them. During the design of our intervention, we could not find any instructionally designed, evidence-based, multimedia e-learning content about dementia risk reduction available in Canada in both languages (English and French). Moreover, very few educational interventions related to dementia risk reduction have been rigorously studied using methods such as randomized controlled trials (RCTs).

While multidomain interventions have been shown to be effective [2], our study will complement those types of more intense, in-person components with a view to expanding awareness of modifiable risk factors to the general population. In addition, while text-based information about risk factors is widely available, DementiaRisk [3]—our instructionally designed, multimedia intervention—is designed to share this knowledge broadly in a way that can improve the understanding of Canadian people. Many interventions about dementia are designed specifically for older adults. However, the development of dementia can begin as early as 20 years before symptom onset or diagnosis [4], so we will be targeting the intervention to all Canadian people of 18 years and older of age to reduce the risk of dementia as early as possible.

A recent EKOS dementia public opinion survey highlighted that there are still many important gaps in the knowledge of Canadian people about dementia risk factors, with only 37% of respondents knowing the link to chronic conditions that affect brain health, such as hypertension, heart disease, and diabetes [5]. Moreover, just over one-tenth believe that hearing loss can increase the risk of developing dementia; and many believe that exposure to toxic chemicals is a risk factor, despite lack of evidence [5].

### e-Learning Instructional Design

DementiaRisk (Figure 1), when compared to other web-based content, is unique because it uses best practices in multimedia e-learning instructional design, is open-access, and includes asynchronous e-learning with email-based microlearning. To our knowledge, it is also the only asynchronous multimedia e-learning dementia education program with French translation available. Key components of the instructional design include the use of the principles of multimedia learning and audio narration; personalization, including the use of a web-based “coach” or embodied instructional agent; segmenting the content into manageable topics to reduce cognitive load; authentic scenarios and worked examples; review questions; and learner control over navigation [6]. An iterative, participatory instructional design and development methodology—the successive approximation method [7]—was used, with extensive involvement and review from a range of experts in dementia care, including care partners.

In this study protocol, we describe a sequential explanatory mixed methods design RCT comparing the efficacy of DementiaRisk, a high-quality, web- and email-based dementia risk reduction education platform that includes asynchronous multimedia e-learning and email-based “microlearning” content, to our alternative web-based learning program on mild cognitive impairment. This study will be an important contribution to the literature on improving knowledge of dementia risk factors through web-based interventions. These innovations are an important complement to traditional approaches to dementia and brain health education, a key component of quality dementia care and public health policy. This is the first research study of the effectiveness of DementiaRisk.

**Figure 1 figure1:**
[figure not shown]
DementiaRisk home page.

### Research Aim

The overall aim of this study is to explore if and how our dementia risk reduction e-learning influences participants’ knowledge, intentions, and health behaviors related to dementia risk factors.

### Specific Objectives

The specific objectives of this study are (1) to evaluate whether exposure to the e-learning intervention changes knowledge of dementia risk factors, intention to engage in risk reduction activities, and health behaviors related to dementia risk reduction and (2) to explore qualitative aspects such as participants’ engagement and satisfaction with the intervention, as well as barriers and facilitators to use, through surveys.

### Research Questions

This study aims to answer the following research questions: (1) Does DementiaRisk increase knowledge of dementia risk factors? (2) Does DementiaRisk increase intentions to engage in risk reduction activities? (3) Does DementiaRisk increase health behaviors related to dementia risk reduction? and (4) Are participants engaged and satisfied with DementiaRisk?

## Methods

### Study Design

A sequential, explanatory, mixed methods design RCT will be conducted to test the effectiveness of DementiaRisk on increasing knowledge, intentions, and behavior change related to modifiable risk factors of dementia. Participants will receive assessments at the following time points: baseline (T1), at 4 weeks (T2), and at 2 months after the intervention (T3; Figure 2). This specific research design offers a valuable approach because it strategically combines the strengths of both quantitative and qualitative research methods.

The underlying philosophy guiding this mixed methods approach is pragmatism, which emphasizes the practical application of research to address real-world problems [8]. This philosophical approach encourages the use of both quantitative and qualitative methods, allowing for more flexibility from other methodological constraints. This flexibility is particularly advantageous in mixed methods research, as it allows us to adapt our approach to capture unexpected findings that may emerge during the study [9]. By incorporating both quantitative and qualitative data, we can gain a more comprehensive and nuanced understanding of the relationship between DementiaRisk and impacts on knowledge, intentions, and behavior change.

**Figure 2 figure2:**
[figure not shown]
Participant flow through the study. MCI: mild cognitive impairment. For a higher-resolution version of this figure, see Multimedia Appendix 1.

### Participants, Setting, and Procedure

#### Overview

Participants will be recruited using AskingCanadians, a paid panel service that can find representative Canadian participants, including those at increased risk of dementia. AskingCanadians was established in 2005 as a web-based data collection firm, which now allows for access to over 1 million Canadian consumers. The panel will send a copy of our recruitment email to their network where interested participants will be redirected to a survey to identify their eligibility. We will ensure a representative sample of diverse participants with key nonmodifiable and modifiable risk factors for dementia, including a greater percentage of women, some participants with lower level of education, and other risk factors such as hearing impairment, hypertension, smoking, alcohol consumption, and others.

#### Inclusion and Exclusion Criteria

Participants are eligible to participate, if they meet the following self-reported inclusion criteria: (1) they do not have a prior diagnosis of dementia, (2) they reside in Canada, (3) they are 18 years and older of age, (4) they have a good command of the English language, (5) they have access to email and high-speed internet, (6) they are comfortable using email and internet, and (7) they have the ability to grant web-based informed consent. Participants are not eligible to participate if (1) they have a prior diagnosis of dementia, (2) they do not reside in Canada, (3) they are not 18 years and older of age, (4) they do not have a good command of the English language, (5) they do not have access to email and high-speed internet, (6) they are not comfortable using email and internet, and (7) they do not have the ability to grant web-based informed consent. Eligibility screening, informed consent, and surveys will be conducted entirely on the web.

#### Randomization and Allocation Concealment

Participants will be randomized and directed to their assigned group after submitting web-based informed consent using the Division of e-Learning Innovation’s research platform. Participants will be randomized using a permuted block stratified randomization, using education and age as the stratification variables. Our stratified block randomization approach will be based on the following components: (1) level of education: we will stratify participants based on educational background or highest level of education completed: “high school or equivalent,” “some college or university,” and “college or university graduate or graduate degree” and (2) age: we will stratify participants based on ages: “younger than 45 years,” “45-65 years,” and “older than 65 years.”

To ensure a balance between the intervention and the control groups, we will use stratified block randomization with variable block sizes of 4, 6, and 8 (randomly arranged) in a ratio of 1:1. To the best of our ability, efforts will be made to blind participants to their allocation group and study hypotheses. We will ensure that promotional advertisements do not contain logos or direct website links. The informed consent form will not contain the exact outcome measures or the title of the intervention. Allocation concealment will be aided by referring to the intervention as “e-learning related to cognitive impairment and dementia prevention” without biasing participants to study hypotheses or study design.

#### Sample Size Calculation

Using a conservative estimate of a small effect size (0.16, from a meta-analysis of internet health behavior change interventions), with a power of 0.80 and α of .05, we require a total of 388 participants in the study [10,11]. To allow for a 25% dropout rate, we aim to recruit 485 individuals [10,11]. These recruitment numbers and strategies have been used successfully in similar knowledge translation intervention studies and are a feasible target, given the use of the paid panel [12].

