#### Primary Outcome

The primary outcome measure of this study is knowledge change related to dementia risk factors. Knowledge of dementia risk factors will be assessed using a custom 15-item multiple-choice assessment aligned with the content of the intervention as well as the risks and health promotion subdomain of the Dementia Knowledge Assessment Scale [13]. Response options are “false,” “probably false,” “probably true,” “true,” and “I don’t know.” The total maximum score for this assessment is 30 (maximum 2 points per question), with higher scores indicating higher levels of knowledge related to dementia risk factors. Individual scoring is as follows: (1) 2 points for answering “true” to a true question, (2) 2 points for answering “false” to a false question, (3) 1 point for answering “probably true” to a true question, (4) 1 point for answering “probably false” to a false question, (5) 0 points for answering “probably false” or “false” to a true question, (6) 0 points for answering “probably true” or “true” to a false question, (7) 0 points for answering “I don’t know.”

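### The stated inputs (effect size 0.16, 80% power, alpha .05, two equal arms) do not yield a total of 388, and the assumptions that would reconcile them are not given

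*Protocol article*

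**What the plan says.** The Sample Size Calculation section of the Protocol article gives a complete power claim: a "small effect size (0.16, from a meta-analysis of internet health behavior change interventions), with a power of 0.80 and α of .05", and from these "we require a total of 388 participants in the study". It then adds an allowance for loss: "To allow for a 25% dropout rate, we aim to recruit 485 individuals".

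The design facts needed to check this are elsewhere in the article. The abstract's Methods say participants are "randomly assigned to 2 groups", and Randomization and Allocation Concealment specifies "variable block sizes of 4, 6, and 8 (randomly arranged) in a ratio of 1:1". Under Primary Outcome, "The primary outcome measure of this study is knowledge change related to dementia risk factors", scored from 0 to 30. Health behaviours are a secondary outcome. The Quantitative Data section plans a linear mixed effects model of score on group by time point, using baseline (T1), 4 weeks (T2) and 2 months after the intervention (T3).

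The sample size paragraph does not name the effect-size metric, the sidedness, the test or any correlation between repeated measurements.

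**The concern.** An effect of 0.16 standard deviations is small. A two-arm trial normally needs well over a thousand participants to detect it with 80% power, so a total of 388 looks too low by a factor of about three.

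What is at stake is how the results are read. Recruitment has closed and the number of participants is fixed. A reader who trusts the paragraph will treat a null result as coming from a trial with an 80% chance of detecting a small effect. If the true power is materially lower, that inference is unsafe. The paragraph also borrows its effect from behaviour-change interventions, whereas the outcome it is meant to power is knowledge.

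**Working it through.** **Inputs.** Effect size 0.16, power 0.80, alpha .05 and total 388 come from Sample Size Calculation. Two arms come from the abstract and 1:1 allocation from the randomisation section, so there are 194 per arm. Assumptions, because the article is silent: 0.16 is a standardised mean difference d (SD = 1), and the test is two-sided unless stated. For repeated measures, T1, T2 and T3 have equal variance and a common correlation ρ.

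**Step 1. Try to reproduce 388.** Per arm, n = 2(1.960 + 0.842)² / 0.16² = 2 × 7.849 / 0.0256 = 613.2, so 614 per arm and 1,228 in total. The exact t calculation gives 614.2 per arm. A one-sided test needs 484 per arm, 968 in total. Neither gives 388.

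**Step 2. Power at 388, single unadjusted comparison.** Power = Φ(d√(n/2) − 1.960) = Φ(0.16 × √97 − 1.960) = Φ(1.576 − 1.960) = Φ(−0.384) = 35% (exact t 34.9%). One-sided power is 47%. Analysing all 485 with no loss would give 42%.

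**Step 3. Gain from baseline and repeated measures.** Replace the variance 1 by a factor v. Power becomes Φ(1.576/√v − 1.960), and the effect detectable with 80% power is 2.802 × √(v/97).
- One follow-up adjusted for baseline: v = 1 − ρ².
- Mean of T2 and T3 adjusted for baseline: v = (1 + ρ)/2 − ρ².

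| Analysis of 388 | ρ | v | Power at d = 0.16 | Detectable d |
|---|---|---|---|---|
| Unadjusted | – | 1 | 35% | 0.285 |
| One follow-up, adjusted | 0.5 | 0.75 | 44% | 0.25 |
| One follow-up, adjusted | 0.7 | 0.51 | 60% | 0.20 |
| T2/T3 mean, adjusted | 0.5 | 0.50 | 61% | 0.20 |
| T2/T3 mean, adjusted | 0.7 | 0.36 | 75% | 0.17 |

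If the contrast is instead a simple change from baseline to one follow-up, v = 2(1 − ρ). Power is then 35% at ρ = 0.5 and 53% at 0.7.

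**Step 4. Correlation needed for 80%.** The required factor is v = 388/1,226 = 0.316. From 1 − ρ² = 0.316, ρ = 0.83. From (1 + ρ)/2 − ρ² = 0.316, ρ = 0.75.

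**Step 5. Other meanings of 0.16.**
- Cohen's f with two groups needs 309, and 388 would give 88%. For two equal groups d = 2f, so f = 0.16 means d = 0.32.
- Cohen's f with 2 numerator degrees of freedom (as for three groups) needs 380, and 388 gives 81%. This is close to 388 but not equal, and the trial has two arms.
- A correlation r = 0.16 needs about 304.
- A repeated-measures interaction formula over three time points with f = 0.08 (half of 0.16) needs 403 at ρ = 0.2 and 353 at ρ = 0.3, so it passes through 388 at a low correlation. For a group difference of 0, d, d at T1, T2, T3, the interaction f is (d/2) × √(6/27) = 0.236d. So f = 0.08 means d = 0.08/0.236 = 0.34, again about twice 0.16.

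**The case against.** The strongest reply is that 35% is not the power of the planned analysis. The article plans a mixed model over three time points, and an unadjusted comparison at one time point is planned nowhere. With both follow-ups and a correlation of 0.75, a standardised difference of 0.16 does reach 80% at 388. The documents give no correlation, so nothing in them rules that value out. The paragraph is also condensed and cites sources that are not shown. If the metric were Cohen's f for two groups, 388 would give more power than claimed, so even the direction of the discrepancy depends on the metric.

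Much of this stands. A reader might infer that the trial's power is simply 35%, or that a true effect of 0.16 would be missed about two times in three. The documents do not support either as a general statement. With the baseline-adjusted mean of T2 and T3, the miss rate is about 39% at correlation 0.5 and 25% at 0.7. For the same reason, replacing 80% with a single figure of 35 to 45% would be too narrow.

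A reader might also infer that the word conservative is wrong because 0.16 is a behaviour effect. That is not established either. If knowledge is easier to change than behaviour, borrowing the smaller effect is cautious, and no document shows the expected knowledge effect.

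The reply does not rescue the printed claim. This is not an objection to an omitted detail: effect, power, alpha and total are all stated, and the total does not follow from the other three. Each route to about 388 needs a correlation that is not stated, a test that does not match two arms, or an effect about twice the one a reader would understand.

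**Conclusion.** The concern holds in this form: the stated inputs do not yield 388, and the claimed 80% power is unsupported as written. On the natural reading of a pooled effect from a meta-analysis of interventions (a standardised mean difference, tested two-sided), about 1,228 participants would be needed for one unadjusted comparison, and 388 is under a third of that.

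Using baseline and repeated measures narrows the gap. Over correlations of 0.5 to 0.7, power at 388 is about 44% to 60% for one baseline-adjusted follow-up and about 61% to 75% for the baseline-adjusted T2/T3 mean. These ranges rest on equal variances, a common correlation and 388 complete cases. The correlations are illustrative assumptions, since the article gives none.

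If Cohen's f was intended, the number is more than sufficient, but for an effect of d = 0.32, and the paragraph must say so. Whether 485 is the right inflation for 25% loss is a separate question and carries no weight here.

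**What to change.** Rewrite the sample size paragraph so that its figures follow from one another:

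- Name the effect-size metric, the sidedness, the test or model contrast, the number of follow-ups used and the assumed within-person correlation.
- If an assumption that gives 388 was made, state it, and say that power falls if the correlation is lower.
- Otherwise correct the claim to what 388 delivers. As a standardised difference, the effect detectable with 80% power is about 0.29 unadjusted. It is about 0.25 (correlation 0.5) to 0.20 (0.7) for one baseline-adjusted follow-up, and about 0.20 to 0.17 for the baseline-adjusted T2/T3 mean.
- State that 0.16 comes from behaviour-change interventions while the primary outcome is knowledge.
- In the report, interpret null results by the confidence interval, not as negatives from a trial with 80% power for 0.16.

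No further enrolment is proposed and nothing in the conduct of the trial changes. The cost is one reworded paragraph and, unless a supporting correlation or a different metric is documented, a less favourable power statement.

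### The target of 485 covers 20% dropout, not the stated 25%; at 25% about 364 participants remain, 24 short of the required 388

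*Protocol article*

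**What the plan says.** The Sample Size Calculation section of the protocol article starts from an effect size of 0.16, "with a power of 0.80 and α of .05", and concludes "we require a total of 388 participants in the study". The next sentence gives the allowance for attrition: "To allow for a 25% dropout rate, we aim to recruit 485 individuals". The Methods paragraph of the Abstract repeats the target as the number randomised: "In total, 485 participants will be recruited on the web and randomly assigned to 2 groups". Allocation is "in a ratio of 1:1" (Randomization and Allocation Concealment).

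The article gives no other dropout rate or recruitment target. Nothing in it suggests that the 25% means anything other than the share of participants expected to be lost.

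**The concern.** A dropout rate is a proportion of those who enter the trial. To keep n participants after losing a fraction d, the trial must enrol n / (1 − d). Multiplying n by (1 + d) always gives a smaller number and leaves the trial short at the very dropout rate it was meant to absorb. The target of 485 looks like the product of that shortcut.

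Two things are at stake. First, the stated 80% power is tied to 388 participants, and the plan does not secure 388 at its own assumed attrition. Second, readers will judge the trial's observed attrition against the published allowance. If loss falls between 20% and 25%, the results paper could say that attrition stayed within plan although fewer than 388 people completed.

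**Working it through.** **Inputs** (all from Sample Size Calculation unless noted)

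- Required number: n = 388
- Dropout rate: d = 0.25
- Recruitment target: 485, also the number randomised (Abstract, Methods)
- Power 0.80 and α 0.05. Sidedness is not stated; two-sided is assumed here.
- Allocation 1:1 (Randomization and Allocation Concealment)

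**Step 1. Reproduce the plan's figure.** n × (1 + d) = 388 × 1.25 = 485. The match is exact.

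**Step 2. Apply the standard formula.** n / (1 − d) = 388 / 0.75 = 517.3, rounded up to 518. The stated target is 518 − 485 = 33 lower.

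**Step 3. Find the dropout that 485 covers.** 1 − 388/485 = 0.20. Put another way, the margin is 485 − 388 = 97 people. That is 25% of 388 but 20% of 485, and the second is the dropout rate.

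**Step 4. Find who remains at the stated rate.** 485 × 0.75 = 363.75, about 364. The shortfall is 388 − 364 = 24, and 24/388 = 6%.

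**Step 5. Translate into power.** Take 388 as giving 80% power, as the article says, for a two-sided comparison of two means with equal groups. Hold the effect fixed. The design's standardised signal is then 1.96 + 0.8416 = 2.8016 at 388, and it scales with the square root of the sample size:

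Power at 364 = Φ(2.8016 × √(364/388) − 1.96) = 0.774.

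| Quantity | As stated | Recomputed |
|---|---|---|
| Dropout covered by 485 | 25% | 20% |
| Target needed for 25% dropout | 485 | 518 |
| Remaining from 485 at 25% dropout | 388 (implied) | about 364 |
| Power at 25% dropout, if 388 gives 80% | 80% (implied) | about 77.4% |

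**The case against.** The arithmetic is not open to dispute, but there is a fair case that it matters little.

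- **Recruitment is over.** It ran from March 28 to April 28, 2023, and the last participants completed the intervention by August 18, 2023. The planning error can no longer change how many were enrolled, and it does not touch the model or the type I error. Precision now depends on the numbers actually retained. This stands, and it makes the point a reporting correction.
- **The primary analysis is a linear mixed effects model on all three time points, run on intention-to-treat data.** Someone lost after the 4-week assessment still contributes baseline and 4-week scores. The article does not say at which assessment the 25% applies. The 77.4% is therefore a completers-only approximation and not the power of the planned analysis. This also stands. However, the sample size section claims no such credit when it inflates 388, and the per-protocol models may keep fewer people.
- **Retention measures are in place.** The article plans a paid panel, automated reminders and compensation, so dropout above 20% is not a given. That is fair. But under Potential Challenges the article also names higher dropout as its first limitation, and none of these measures adds a numerical margin.
- **The power figure assumes that 388 gives 80% power.** The article does not state the metric of the 0.16, and 388 could not be reproduced from it under the variants tried for two arms. Read as a standardised mean difference it needs 1,228 in total (two-sided); read as Cohen's f with two groups it needs about 308. This is a separate, open question. It is a good reason not to publish 77% as a new figure, but it does not affect Steps 1 to 4.

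None of these points makes 485 the right target for 25% dropout.

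**Conclusion.** The concern holds. The figure of 485 protects 388 against 20% loss and no more. At the stated 25% the trial would keep about 364, which is 24 (6%) below its own requirement, and the target consistent with 25% is 518.

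These counts rest only on numbers in the article and on the ordinary meaning of a dropout rate. The power loss of about 2.6 percentage points (80% to 77.4%) is conditional: it assumes that 388 delivers 80% power, a two-sided 1:1 comparison, and no information from those who drop out. The consequence is modest and does not threaten the trial's validity, but the sentence is wrong as written.

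**What to change.** Correct the sentence in Sample Size Calculation. Keep the 25% on record as the rate originally assumed, because replacing a prospective assumption after follow-up would itself mislead. Suggested wording: *The recruitment target of 485 was obtained by adding 25% to the required 388. It covers a dropout rate of 20% (485 × 0.80 = 388); at 25% dropout about 364 participants would remain.*

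Use the corrected allowance in the results paper, and report actual retention by group at 4 weeks and at 2 months after the intervention, so that attrition is compared with 20% and completers with 388. If a power figure is wanted, give it only with its assumptions stated.

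The cost is one sentence and a slightly less favourable statement of the dropout allowance. No further enrolment and no change to the analysis are needed.
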